# A double-blind clinical trial to compare the efficacy and safety of a multiple amino acid-based ORS with the standard WHO-ORS in the management of non-cholera acute watery diarrhea in infants and young children: “VS002A” trial protocol

**DOI:** 10.1186/s13063-022-06601-5

**Published:** 2022-08-25

**Keywords:** VS002A, WHO-ORS, Diarrhea, Randomized, Amino acid-based ORS

## Abstract

**Background:**

Diarrhea is the second deadliest disease for under-five children globally and the situation is more serious in developing countries. Oral rehydration solution (ORS) is being used as a standard treatment for acute watery diarrhea for a long time. Our objective is to compare the efficacy of amino acid-based ORS “VS002A” compared to standard glucose-based WHO-ORS in infants and young children suffering from acute non-cholera watery diarrhea.

**Methods:**

It is a randomized, double-blind, two-cell clinical trial at Dhaka Hospital of icddr,b. A total of 312 male children aged 6–36 months old with acute non-bloody watery diarrhea are included in this study. Intervention arm participants get amino acid-based ORS (VS002A) and the control arm gets standard glucose-based WHO-ORS. The primary efficacy endpoint is the duration of diarrhea in the hospital.

**Discussion:**

Oral rehydration therapy (ORT) with the present ORS formulation has certain limitations - it does not reduce the volume, frequency, or duration of diarrhea. Additionally, the failure of present standard ORS to significantly reduce stool output likely contributes to the relatively limited use of ORS by mothers as they do not feel that ORS is helping their child recover from the episode of diarrhea. Certain neutral amino acids (e.g., glycine, L-alanine, L-glutamine) can enhance the absorption of sodium ions and water from the gut. By using this concept, a shelf-stable, sugar-free amino acid-based hydration medicinal food named ‘VS002A’ that effectively rehydrates, and improves the barrier function of the bowel following infections targeting the gastrointestinal tract has been developed. If the trial shows significant benefits of VS002A use, this may provide evidence to support consideration of the use of VS002A in the present WHO diarrhea management guidelines. Conversely, if there is no evidence of benefit, these results will reaffirm the current guidelines.

**Trial registration:**

ClinicalTrials.gov NCT04677296. Registered on December 21, 2020.

**Supplementary Information:**

The online version contains supplementary material available at 10.1186/s13063-022-06601-5.

## Background

Diarrheal disease is the second deadliest disease for under-five children globally and the situation is more serious in developing countries. Oral rehydration solution (ORS) is being used as a standard treatment for acute watery diarrhea for a long time [1]. The ORS currently recommended by the WHO/UNICEF contains glucose, sodium chloride, potassium chloride, and tri-sodium citrate dehydrate, which is optimal for rehydration of patients of all ages with dehydration from acute diarrhea of any etiology [2]. However, the present ORS formulation has certain limitations [3]. It does not reduce the volume, frequency, or duration of diarrhea. Additionally, the failure of present standard ORS to reduce dramatically stool output likely contributes to the relatively limited use of ORS by mothers as they do not feel that ORS is helping their child from the episode of diarrhea [4]. Thus, it warrants the development of a newer and improved formulation of ORS to become more effective against diarrhea.

Adding neutral amino acid or their peptides can enhance the absorption of sodium ions and water, an approach to developing an improved ORS formulation by adding neutral amino acid or their peptides to WHO-ORS [5]. Enterade® is a proprietary blend of five amino acids (threonine, valine, serine, tyrosine, and tryptophan) that acutely restores water and electrolyte losses by facilitating intestinal sodium and water transport with similar stoichiometry to glucose [6], but without stimulating chloride secretion like glucose [7]. Based on previous findings regarding amino acid-based ORS, a sugar-free self-stable amino acid-based hydration medicinal food named VS002 was developed, which effectively rehydrates and improves the barrier function of the bowel following infections targeting the GI tract [8]. By using this concept, the University of Florida (UF), developed a sugar-free, shelf-stable amino acid-based hydration medicinal food named “VS002A” that effectively rehydrates, and improves barrier function of the bowel following infections targeting the gastrointestinal tract. So, we aimed to know whether VS002A will be superior or not to WHO-ORS in the treatment of acute non-cholera watery diarrhea in infants and young children.

### Gut health biomarkers

Diarrheal disease among under 5 children contributes to 43% of stunted growth and impaired cognitive development, affecting one-fifth of children worldwide and one-third of children in low- and middle-income countries (LMICs) [9, 10]. A vicious cycle of enteric infection and malnutrition often leads to enteropathy for extended periods in young children [9, 11]. This type of enteropathy is known as environmental enteric dysfunction (EED). EED is a sub-acute inflammatory condition of the small intestinal mucosa of unknown etiology [12]. It is characterized by structural changes in the small intestine including villous atrophy and crypt hyperplasia compromising nutrient absorption and pathogenic barrier (increased permeability and inflammatory cell), impaired gut immune function, malabsorption, growth faltering, and generally asymptomatic, as distinct from the diarrheal disease [11, 13]. Citrulline (CIT) is an amino acid produced by intestinal epithelial cells and found lower in patients with enteropathy [14]. Tryptophan (TRP), a plant-derived essential amino acid (EAA) is needed to support growth and health in humans. In response to infection, TRP is mostly catabolized by an enzyme indoleamine 2,3-dioxygenase (IDO) to toxic metabolite kynurenine (KYN). Low plasma TRP, high KYN, and elevated tryptophan-kyanurenine (KT) ratio are found to be associated with infections and chronic immune activation [10].

Data are limited from LMICs including Bangladesh on inflammatory and pathological changes in the gut wall like EED among children with diarrhea. In this study, we also evaluate plasma CIT concentration as a potential marker of functional enterocyte mass and absorptive functions of the intestine, and KT ratio as a marker of gut inflammation.

## Methods

### Aim

The main aim of the VS002A trial is to compare the efficacy (duration of diarrhea, stool output, ORS intake, and clinical success) of amino acid-based ORS “VS002A” compared to standard glucose-based WHO-ORS (GORS) in infants and young children suffering from acute non-cholera watery diarrhea in a superiority trial. We specify our objective as (i) to evaluate and compare clinical responses (duration of diarrhea [primary end point], stool output, ORS intake, and clinical success [exploratory endpoints]) in infants and young children suffering from acute non-cholera watery diarrhea treated with standard glucose-based WHO-ORS and amino acid-based ORS “VS002A” in a superiority trial and (ii) to evaluate and compare exploratory endpoints of electrolyte imbalance as possible complications in infants and young children suffering from acute non-cholera watery diarrhea treated with standard glucose-based WHO ORS and amino acid-based ORS “VS002A.”

We have our secondary objective to investigate the plasma concentration of CIT and KT ratio among the children having dehydrating diarrhea and examine associations between concentrations of CIT and KT ratio with concurrent factors.

### Study design

The VS002A trial is a randomized, double-blind, two-cell superiority clinical trial comparing WHO-ORS and VS002A conducted in 312 male children aged 6–36 months, presenting with non-bloody acute non-cholera diarrhea with some dehydration in the Dhaka Hospital of icddr,b.

The trial protocol was developed by the investigators of icddr,b, Nutrition and Clinical Services Division, Dhaka Bangladesh together with Entrinsic Bioscience. The study design is described in Fig 1.

**Fig. 1 Fig1:**
[figure not shown]
VS002A trial study design

### Study setting and population

The study is implemented in Dhaka Hospital of icddr,b. The study subjects are 312 male children (to facilitate separate collection of urine and stool), admitted to Dhaka Hospital of icddr,b.

### Inclusion criteria

Age: 6–36 monthsDuration of diarrhea ≤48 hSome dehydration (judged clinically according to the “Dhaka method”) [15]Written informed consent by either parent/guardian

### Exclusion criteria

Severe malnutrition (weight-for-length WLZ/weight-for-height WHZ/weight-for-age WAZ <−3 or presence of nutritional edema)Patients with diarrhea due to choleraSystemic illness (e.g., pneumonia, tuberculosis, enteric fever, and meningitis)Bloody diarrheaAny congenital anomaly or disorder (e.g., diagnosed inborn error of metabolism, congenital cardiac disease, seizure disorders, hypothyroidism, and Down’s syndrome)Requirement of additional intravenous fluids after being provided with an IV for 4 h on admission if severely dehydratedHas documentation of taking antibiotics and/or antidiarrheal within the last 48 h before hospitalization.

### Implementation plan

#### Screening and enrollment procedures

All male children aged 6–36 months, presenting with diarrhea (onset ≤48 h) and some dehydration are screened by the study nurses in the Dhaka Hospital of icddr,b (triage/OPD/short stay ward) for possible inclusion in the study. After getting verbal consent from the parents, all screened children are kept in the Clinical Research Ward for conducting the following activities:A thorough clinical history and physical examination are done, and body weight and height are measured.Correction of some dehydration: The child receives standard WHO-ORS for correction of dehydration, 50–75 ml/kg over 4 h, according to the rehydration protocol followed at icddr,b [2]. During this period, cholera cases are detected using a rapid screening test “Cholkit” [16], conducted by a Study Nurse.

#### Consent

After confirming eligibility, the accompanying primary caregiver is provided written informed consent for the Cholkit test. When the Cholkit test result is negative, the caregiver is provided with another written informed consent for the main trial. For illiterate caregivers, documented witnessed verbal consent and a thumbprint are obtained. During consent, the purpose of the study, as well as all the study procedures, and possible risks are explained to the caregiver by a member of the trial team in the local language. Consent is taken for the collection and storage of and use of samples collected. Caregivers are also informed that they can choose to participate in the trial but not provide samples or they can withdraw their participation at any time after enrollment in the study.

#### Sequence generation

Upon meeting eligibility criteria for the study and after obtaining written informed consent, the subjects are individually randomized into one of the two study groups, VS002A vs. WHO-ORS, through a variable permuted block procedure. Enrolled patients then receive an identification number according to their order of admission in the study. Subjects are then randomized into one of the four groups, using a predefined allocation table. Enrolled patients receive the serially numbered test product that corresponds to their identification number.

#### Allocation concealment

Envelopes containing the treatment allocation are opened by the study physician on participant enrolment. To be robust, the envelopes will be truly opaque, sequentially numbered, and opened in the correct order. Treatment allocation (once assigned) will remain blinded to the participant, the site Principal Investigator, co-Investigators, the site study staff, and the study physicians during all data collection phases of the study.

#### Blinding (masking)

Entrinsic Bioscience blinds the study product. The study products (VS002A and WHO-ORS) are packaged in 310 mL Tetra Pak cartons made indistinguishable except for randomized manufacturer serial numbers broken out into 2 groups, with 2 separate lot numbers per treatment group identifiable by their serial number prefix (e.g., D-XXXX; G-XXXX; O-XXXX; U-XXXX). The entire product group consists of either VS002A or the WHO-ORS. A master file linking groups to product identity is generated; one kept by a single individual at Entrinsic Bioscience and one kept by the Senior Pharmacist of icddr,b pharmacy. The identity of the specific product is blinded to the subjects, the icddr,b Dhaka Hospital staff, sponsor, and the investigators. Patients are truly blinded to the interventions due to similar color, smell, taste, and flavor (citrus) between VS002A and WHO-ORS. The final unblinding of product categories will occur only after statistical analysis.

#### Treatment procedures

The study patients are placed on diarrhea cots. Initial treatment dosing with WHO-ORS or VS002A is estimated using bodyweight following 5–10 ml/kg after each loose stool as per icddr,b guideline, to maintain the ongoing loss. Adjustments may be required and hydration is maintained using smaller or larger volumes depending on measured losses. Children are fed using a spoon. Assessment and treatment are to continue until the resolution of diarrhea. The child is supplemented with tablet zinc: one tablet (20 mg) per day for 10–14 days [2].

In young children who cannot control micturation, a pediatric urine collection (PUC) bag is applied to facilitate the separate collection of stool and urine.

The patient receives liquid, semi-solid, and solid foods appropriate for age. Breast-fed children continue to receive breast milk. If stool culture reveals any pathogen, then the patients receive an appropriate antibiotic if applicable and are excluded from the study (e.g., azithromycin in cholera). Intakes of ORS, food, and medicines are supervised by a nurse and are recorded. Vital signs are recorded for each patient every 4 h. Intake of ORS and water is recorded every 4 h while outputs of stool and urine and vomitus, and stool frequency are recorded continuously. Clinical assessment of the study children is performed by the study investigators and/or designated research physicians. Vital signs and body weight are measured and recorded by experienced nurses of the Study Ward. And other measurements, e.g., stool frequency and volume/weight, intake of rehydration fluids, and urine outputs are measured by designated health workers under the supervision of the study nurse who would record them. Each participating child is closely monitored for the occurrence of any adverse events such as worsening diarrhea or increased vomiting, and their severity and duration are noted and information is also recorded for analysis.

#### Standard management

All two groups will receive standard of care for diarrheal disease, including zinc, rehydration, and nutritional counseling following WHO guidelines. Children with some dehydration will be rehydrated and stabilized. As part of standard case management, caregivers will be advised to seek care immediately if their child is unable to drink or breastfeed, develops a fever, starts passing blood in the stools with continued diarrhea, or becomes sicker.

#### Post-trial care

In addition, as per standard WHO guidelines, the caregiver will also be advised to bring their child back to the health facility if the child’s clinical status is deteriorating after discharge from the hospital for further treatment.

### Dissemination policy

We will be planning to disseminate the result of the trial findings to international and national scientific members and policymakers of the Bangladesh Government after the completion of the trial. And we will plan to publish our study findings in international peer-reviewed journals.

### Outcomes

#### Primary outcomes

Duration of diarrhea in hospital (hours)

#### Exploratory outcomes

Stool output in the 1st 24 h of hospitalization (g/kg body wt.), further divided into two 12-h periodsTotal stool output during hospitalization (g/kg body wt.)ORS intake in the 1st 24 h of hospitalization (g/kg body wt.)Total ORS intake (ml/kg body wt.)Unscheduled IV (frequency/ORS group)Treatment failure (frequency/ORS group)Output and frequency of vomitingChange in body weight (between pre-randomization and post-treatment)Urine output in the 1st 24 h of hospitalization (g/kg body wt.)Total urine output during hospitalization (g/kg body wt.)Documented infectious agentBlood chemistry (between pre-randomization and after 24 h of treatment)Gut health biomarker: citrulline (CIT) and kynurenine to tryptophan ratio (KT) between pre-randomization and at 24 hours after the enrolment)

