### Trial assessments

Children enrolled in the trial are followed up for up to 120 h post-enrolment or until the first primary endpoint is reached which means diarrhea resolution, whichever is earlier. The schedule of enrolment, intervention, and outcome assessments is shown in Table 2, which follows the SPIRIT (statement provides evidence-based recommendations for the minimum content of a clinical trial protocol) guidelines Table 4.

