### Discontinuation procedure

#### Criteria for removal from study and treatment failure

Patients are discharged from the hospital when diarrhea is resolved (the working definition of resolution of diarrhea has been mentioned below). However, no participants are discharged before 24 h from enrolment.If it takes more than 5 days (≥ 120 h) to resolve diarrhea or if a patient becomes dehydrated requiring unscheduled IV fluids, we transfer the patient to the general in- patient’s ward for further evaluation and treatment. In that case, it is considered a “treatment failure.”After enrollment, if any patient develops any co-morbidity like pneumonia, sepsis, electrolyte imbalance or requires specific antibiotics and/or special attention/intervention, we transfer the patients to the General ward or ICU of the hospital and are removed from the study. The reason for removal is recorded and an off-study document is completed by the study team.Patients who decide to withdraw from the study are defined as “drop-out.”Patients who do not consume at least 80% of ORS offered are considered “non-compliant”.If stool culture reveals an agent that needs antibiotic therapy, the patient is removed from the study, and an off-study document is completed by the study team.All data collected on randomized subjects are kept for intent-to-treat analysis, including patients who withdrew from the study (drop out), have co-morbidity, or are defined as treatment failures or non-compliant.

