#### Definitions

Duration of diarrhea in hospital: time in hours, from randomization till resolution of diarrhea.Resolution of diarrhea: the passage of the last liquid or semi-liquid stool before one soft/formed stool or no stool for 12 h [18].Stool output: The weight of stool in g/kg of admission body weight expressed per time period (i.e., per 24 h and for the entire duration of diarrhea).ORS and plain water intakes: The total volume (in ml) of ORS or plain water is taken per kg of admission body weight, expressed per time period.Treatment failure: If diarrhea continues for more than 120 h after enrollment, or requires unscheduled IV fluids due to progressive dehydration, requiring transfer to the general in-patient wardUn-scheduled IV: When intravenous rehydration fluids are given due to the inability of the ORS to maintain hydrationNon-compliance: inability to consume ≥ 80% of ORS

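### Total urine output is summed over a stay that ends when diarrhea resolves, so a between-arm difference mixes urine rate with the primary outcome and has no clear direction of benefit

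*Protocol article*

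**What the plan says.** The primary outcome is "Duration of diarrhea in hospital (hours"), defined under Definitions as "Duration of diarrhea in hospital: time in hours, from randomization till resolution of diarrhea".

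The end of observation depends on the same event in three places:
- Treatment procedures: "Assessment and treatment are to continue until the resolution of diarrhea".
- Trial assessments: children are "followed up for up to 120 h post-enrolment or until the first primary endpoint is reached which means diarrhea resolution, whichever is earlier".
- Criteria for removal from study and treatment failure: "Patients are discharged from the hospital when diarrhea is resolved", although "no participants are discharged before 24 h from enrolment".

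The Exploratory outcomes list gives urine output in two forms. One has a fixed window, "Urine output in the 1st 24 h of hospitalization (g/kg body wt".). The other is the stay total, "Total urine output during hospitalization (g/kg body wt".). Neither has an entry under Definitions, and no form per hour or per day is given for the total. The same list has a change in body weight from before randomization to after treatment, with no stated hour for the second weighing.

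**The concern.** A stay total is a rate multiplied by a length of observation, and here the length of observation is largely the primary outcome. Two children who pass urine at the same hourly rate will have different totals if one recovers sooner, and the one who recovers sooner has the lower total. A difference between arms therefore cannot be attributed to urine rate, to duration, or to a given mixture of the two.

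Total stool output and total ORS intake share this window, but lower stool loss or lower ORS need over an episode can be read as a benefit in itself. A lower urine total that comes only from earlier discharge is neither benefit nor harm. The distortion also appears in exactly the situation the trial hopes to find, a shorter illness on VS002A. What is at stake is the reading of one exploratory outcome.

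Weight change has a related but weaker problem. It is a difference between two readings, not a running sum, but the second reading falls at a time set by the outcome.

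**Working it through.** The article prints no figure for urine output or weight change, so there is none to reproduce.

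**Inputs from the article.** Target effect: a 20% improvement in duration (Sample size and power). Stay limits: 24 h and 120 h. Evaluable children: 132 per group. Placebo durations in Table 3: mean 5.73 days with pooled SD 1.62, and mean 4.7 days with pooled SD 2.15.

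**Assumptions not in the article.** Equal mean hourly urine rate in both arms; log-normal durations; every VS002A duration scaled by 0.8; two shorter control scenarios, 3 days (SD 1.5) and 2 days (SD 1.0); stay equal to duration, clipped to 24 to 120 h.

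**Formula.** Ratio of totals (VS002A / WHO-ORS) = hourly rate ratio × ratio of mean stays.

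**Without limits.** 1.00 × 0.80 = 0.80. The break-even rate ratio is 1 / 0.80 = 1.25.

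**With the 24 h and 120 h limits (simulation):**

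| Control duration | Mean stay, WHO-ORS (h) | Mean stay, VS002A (h) | Ratio of totals at equal rate | Break-even rate ratio | Ratio of totals at rate ratio 1.25 |
|---|---|---|---|---|---|
| 5.73 days | 112.9 | 101.7 | 0.90 | 1.11 | 1.13 |
| 4.7 days | 96.1 | 83.3 | 0.87 | 1.15 | 1.08 |
| 3 days (assumed) | 69.0 | 56.8 | 0.82 | 1.22 | 1.03 |
| 2 days (assumed) | 48.2 | 39.5 | 0.82 | 1.22 | 1.03 |

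For example, 101.7 / 112.9 = 0.90. At equal hourly output the VS002A total is therefore about 10% to 18% lower. Dividing each child's total by the hours observed, or using the fixed first 24 h, gives a ratio of 1.00 in every row.

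**Would it be noticed?** With 132 per group and an assumed between-child coefficient of variation of 40% in hourly rate, the chance of a significantly lower VS002A total (z below −1.96) with no true rate difference is 49%, 64%, 75% and 72% in the four rows. These chances depend on the assumed 40%.

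**Weight change.** The article gives no weight trajectory, so no size can be computed. A shorter stay leaves less time for regain, while smaller stool losses act in the opposite direction. The baseline is also not tied to a time. Weight is measured at screening, where 50–75 ml/kg of WHO-ORS is also given over 4 h. At 1 g per ml that intake is 5% to 7.5% of body weight, given to both arms before allocation. If the weight before it is the baseline, the change includes part of that fluid.

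**The case against.** A reader might infer that a product that shortens diarrhea will necessarily look worse on hydration. The article does not support that. The break-even column shows that an hourly rate 11% to 22% higher on VS002A cancels the deficit, and better absorption could plausibly raise the rate. At a ratio of 1.25 the total favors VS002A. Transfers and removals may also shorten the window for reasons other than recovery.

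A reader might also infer that weight change has the same fault with the same sign. It does not, for the reasons given in the check. The figure with the schedule of assessments is not available here, so a 24-h weighing may already be planned.

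The size is easy to overstate. The 20% target applies to duration, not stay, and both limits dampen it. Resolution is dated to the last liquid or semi-liquid stool but may need 12 stool-free hours to confirm, so stay can exceed duration. Roughly, adding 12 h to both means in the 3-day row gives (56.8 + 12) / (69.0 + 12) = 68.8 / 81.0 = 0.85 instead of 0.82. The five-fold range from 24 h to 120 h is a spread between children, not a bias between arms.

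Finally, the article neither calls these items hydration endpoints nor states a favorable direction. It already lists a fixed-window urine value and captures failure to maintain hydration through unscheduled IV fluids and treatment failure. All of this stands and makes the point small. It does not make the stay total interpretable, and the total is stated explicitly in this form, so it is not merely a detail left to an analysis plan.

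**Conclusion.** The point holds for total urine output. Its window is largely set by the primary outcome, so a between-arm difference confounds urine rate with duration. At equal hourly rates and a 20% shorter duration, the VS002A total may be about 10% to 18% lower without any difference in hydration. That range rests on the assumed duration distributions and on stay equal to duration within the 24 h and 120 h limits. The net direction in the real data is unknown because the hourly rate in each arm is unknown.

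For weight change, only the weaker statement holds: the second reading is taken at an outcome-dependent time, and the direction of any bias cannot be determined from the article. Unlike urine output, it has no fixed-time companion in the outcomes list.

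Both are exploratory, so the primary analysis, sample size and primary conclusion are unaffected. This is a cheap improvement, not a flaw in the trial's main comparison.

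**What to change.** In Exploratory outcomes:

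- Replace the stay total of urine, or accompany it, with urine output per kg per hour of observation from randomization.
- Name the already listed first-24-h urine value as the one to rely on when the arms are compared.
- Add a weight change at a fixed time: weight 24 h after randomization, in children still under observation, minus a weight taken at randomization after the 4-h rehydration. Keep the end-of-treatment weight as descriptive.

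Urine output is already recorded continuously, so the first change costs one division by recorded hours. Nurses already weigh the children, so the weight change adds at most one scheduled weighing and slightly more analysis. Children withdrawn, transferred or removed before 24 h will lack the 24-h values, and their number should be reported by arm.
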